### Randomization

#### • Clinicians

Clinicians who have consented to participate will be randomly allocated, by computer-generated codes (code: exercise questionnaire group (EQ); no exercise questionnaire group (NQ)) in sealed opaque envelopes, to one of two groups with stratification to allow equal representation of qualifications. These codes will be generated by an independent researcher who has no contact with trial participants. Group 1 clinicians allocated to use the exercise preferences questionnaire will use the responses to the exercise preferences questionnaire to inform their exercise prescription. Group 2 clinicians do not use the exercise preferences questionnaire and will return the unopened envelope to a secure storage box in the reception area. These clinicians will prescribe exercise according to their usual practice.

The two groups of clinicians will not disclose their group allocation or any details or findings of the questionnaire. A code-breaker master document will be kept in a locked location at the university and cannot be viewed by reception staff or clinicians.

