Following Monash University Standing Committee on Ethics in Research Involving Humans (SCERH) approval (SCERH CF07/1854 – 2007/0558), we conducted qualitative focus group research of participant experience of exercise programs for NSCLBP and factors that they perceived important for engagement and participation. The results of this study indicated that people with NSCLBP have a range of environmental and exercise design preferences that are important to consider in exercise prescription. Enablers for exercise participation included shared decision-making, effective communication, a history of exercise ability and participation, familiarity with exercise environments and the fitness culture, individualised and supervised programs, use of preferred environments, family support, variety and fun, motivation strategies and education. Barriers included time constraints, cost, boring programs, symptom aggravation, consequences of stigma, dissatisfaction with formal exercise and gym 'culture' [23-25].

A decision-aid for exercise prescription is currently not available and the results of our qualitative research have informed the development of a questionnaire that clinicians can use to determine participant exercise preferences and inform their practice of exercise prescription. This questionnaire requires testing in the clinical environment to determine its utility as a method of systematic evaluation of care-seeker needs and preferences related to exercise. The research plan is to implement the questionnaire in a range of exercise programs that are specific to NSCLBP, evaluate the effectiveness of individualised exercise prescription and evaluate feedback about the instrument.

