### Study population and recruitment

#### • Clinics and clinicians

The study will be conducted in Melbourne metropolitan primary health care clinics that provide exercise programs for rehabilitation of musculoskeletal conditions. The contact details used will be those publicly available in the telephone directory or online at professional association websites. The clinics will be approached by telephone or email/mail advertisement seeking expressions of interest in research participation.

A phone conversation or meeting will be scheduled with the practice principal to outline the project and distribute the Explanatory statement and Clinic Consent Form. After receipt of signed Clinic Consent, information sessions will be scheduled to address clinicians and inform them of the research background and aims. They will be given an Explanatory Statement to read and keep and a Clinician Consent Form to sign and return to the researcher if they wish to participate. Reception staff in-service training will also be conducted to familiarize clinic staff with the recruitment process, paperwork completion and filing.

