### Concealment

#### • Patients and receptionists

If patients are eligible and interested, reception staff will give them the Explanatory Statement to read and keep and a Consent Form that they will sign and return to the receptionist for filing. Following signed consent participants will complete coded outcome measures and exercise preference questionnaires and return them sealed to reception staff for storage in a secure box for retrieval by the researcher. The completed exercise preferences questionnaire will be put in a sealed envelope, marked EQ, and forwarded to the treating clinician. The envelope will only be opened by the clinicians allocated to the questionnaire group. Reception staff and patients will not know which practitioners have been allocated to use the completed exercise preference questionnaire to guide exercise prescription or to the control group.

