### Sample Size

A total of 120 patients (60 questionnaire group, 60 no questionnaire group) will be required for 80% power to detect a 5 point reduction on 100 point measure of function with 95% confidence using a two-tail test of difference between group means when raw scores have an estimated standard deviation of 10/100 points). We will allow for a 10% loss to follow-up and aim to recruit 75 participants per group. This will enable collection of data for at least 85% of enrolled participants.

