### Data Analysis

Analysis will be by intention to treat. As scores are expected to improve across time, missing data will be replaced by the last score carried forward. If mean scores deteriorate across time, missing data will be replaced by the last score minus the reduction in scores anticipated using trend analysis of previous scores. Demographic characteristics and baseline data will be summarised by descriptive statistics. Distributions of all continuous data will be assessed for normality. Between-group comparisons of normally distributed data will be performed with independent t tests. Non-normally distributed data will be compared with the Mann Whitney U statistic. Relative risks and their 95% confidence intervals will be used to report group differences in proportions for similar outcomes. Continuous variables will be assessed for relationships between baseline scores and outcome. If a significant relationship is found, analysis of covariance (ANCOVA) will be conducted to test the effect of the intervention when controlling for the confounding effects of baseline scores on outcome. Effect sizes with 95% confidence intervals will be calculated for pain and function measures.

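### Clinician allocation is not stated to be balanced within clinic and the planned tests carry no clinic or clinician term, so chance imbalance between clinics adds variance that the analysis does not count

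*Protocol article*

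**What the plan says.** All references are to the protocol article.

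- **Setting and recruitment (Clinics and clinicians).** Several clinics are used: "The study will be conducted in Melbourne metropolitan primary health care clinics that provide exercise programs for rehabilitation of musculoskeletal conditions". The clinic agrees first and its clinicians follow: "After receipt of signed Clinic Consent, information sessions will be scheduled to address clinicians".
- **Unit of allocation (Randomization).** "Clinicians who have consented to participate will be randomly allocated, by computer-generated codes", "to one of two groups with stratification to allow equal representation of qualifications". No other restriction on the allocation is named.
- **Both arms under one roof (Concealment).** "Reception staff and patients will not know which practitioners have been allocated to use the completed exercise preference questionnaire". The sealed-envelope procedure and the non-disclosure rule allow both arms to sit in one clinic, but nothing secures it.
- **Analysis (Data Analysis).** "Between-group comparisons of normally distributed data will be performed with independent t tests". ANCOVA on the baseline score follows if baseline and outcome are related. Neither clinic nor clinician enters.
- **Size (Sample Size).** "A total of 120 patients (60 questionnaire group, 60 no questionnaire group) will be required for 80% power", for a 5-point difference with SD 10, two-sided at 5%. The recruitment target is 75 per group.

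**The concern.** Clinicians who share a clinic also share its facilities, fees, patient mix and local habits. The Background reports from the team's own focus groups that "people with NSCLBP have a range of environmental and exercise design preferences that are important to consider in exercise prescription", and it lists cost and gym culture among the barriers. It is therefore plausible, though not shown, that outcomes differ between clinics.

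If the allocation does not balance arms within clinic, part of any difference between clinics passes into the arm contrast. The t test computes its standard error as if patients were independent, so it does not see this component. Two things are at stake: precision, because the estimate varies more than it needs to, and validity of the p-value, because the reported standard error is too small.

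**Working it through.** **1. The plan's own figure.** Patients per arm = 2 × (1.96 + 0.842)² × 10² / 5² = 62.8, so 63 per arm or 126 in all. The stated 60 per arm gives 78.2% power. The plan is thus close to its 80% if patients are independent. For 150 patients under independence the SE is √(4 × 100/150) = 1.63 points, which is about what the t test will report.

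**2. How often a clinic falls wholly in one arm.** For a clinic of m clinicians under simple allocation the probability is 2 × (1/2)^m: 50% for m = 2 and 12.5% for m = 4. With arms balanced over 10–30 clinicians it is 44–48% for m = 2 and 5–10% for m = 4. Stratification by qualification changes this. If both clinicians of a clinic share a qualification and each qualification has four clinicians split 2:2, it is 1/3. If they have different qualifications, it is 1/2.

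**3. Standard error of the arm difference.** Assumptions not in the article: 20 clinicians in 10 clinics of two, 7.5 patients each, clinician ICC 0.03, clinic ICC 0.02, 0.05 or 0.10. With total variance 100, V_clinic = 2/5/10, V_clinician = 3 and V_error = 95/92/87.

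Var = (4/20) × [c × V_clinic + V_clinician + V_error/7.5]

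- 10:10 allocation ignoring qualification: c = (20/19)(1 − 2/20) = 0.947.
- Qualification strata of four, single-qualification clinics: c = (4/3)(1 − 2/4) = 0.667.
- Balanced within clinic: c = 0.

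Example for clinic ICC 0.05, ignoring qualification: 0.2 × (4.74 + 3 + 12.27) = 4.00, so SE = 2.00.

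| Clinic ICC | SE, ignoring qualification | SE, qualification strata | SE, within clinic |
|---|---|---|---|
| 0.02 | 1.87 | 1.84 | 1.77 |
| 0.05 | 2.00 | 1.93 | 1.75 |
| 0.10 | 2.19 | 2.06 | 1.71 |

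If the two clinicians of each clinic have different qualifications, c = 1 and the SE at ICC 0.10 is √[0.2 × (10 + 3 + 11.6)] = 2.22, which is 0.03 above the top of the table.

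**4. Type I error of the planned t test.** The t test's expected SE in these layouts is 1.62–1.63. Type I error is approximately 2 × Φ(−1.96 × t-test SE / true SE).

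| Clinic ICC | Ignoring qualification | Qualification strata | Within clinic |
|---|---|---|---|
| 0.02 | 8.9% | 8.3% | 7.1% |
| 0.05 | 11.1% | 9.8% | 6.8% |
| 0.10 | 14.8% | 12.3% | 6.3% |

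A simulation of the same layouts agreed within one percentage point, and the mean estimated effect under the null was about zero in every case.

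**5. Larger clinics.** One-armed clinics are rarer with four clinicians each, but uneven splits remain and the variance term shrinks little: c = (20/19)(1 − 4/20) = 0.842.

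**6. What clinic balancing does not do.** Type I error stays above 5% in the last column because clinicians are the randomised unit and their own variance is still ignored. A random effect for clinic alone does not help: its model SE is about 1.6 against a true 1.75, which leaves about 7%.

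**The case against.** A reader might infer that clinic is confounded with the intervention. The article does not support that. Clinicians are randomised individually, so clinic is not linked to arm by design, and the simulations show no systematic bias. What remains is chance imbalance and uncounted variance.

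Other objections have weight:

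- **The inputs are assumed.** The article gives no number of clinics, clinicians per clinic or ICC. A single-clinician clinic stays in one arm under any scheme. The sizes are illustrations.
- **Qualification strata may help incidentally.** Where a clinic houses one profession, stratifying by qualification partly balances clinic too. A gain computed against wholly unstratified allocation, such as power rising from 63% to 83% at clinic ICC 0.10, overstates the case: with the qualification strata above, the starting point is 68%.
- **The Background reports perceived enablers and barriers to exercise participation.** It does not show that clinics differ in disability scores.
- **The article is condensed.** A fuller protocol could name a further factor. But the article does state its allocation restriction and its tests, and neither mentions clinic.
- **Contamination.** Balancing within clinic puts both arms in every multi-clinician clinic. Suppose contamination cuts the 5-point effect by 20% in mixed clinics. Without clinic balancing 10/19 of clinics are mixed, so the mean effect is 5 × (1 − 0.2 × 10/19) = 4.47; with it, 4.00. Power, Φ(effect/SE − 1.96), goes from 67% to 62% at clinic ICC 0.02, from 61% to 63% at 0.05 and from 53% to 65% at 0.10. With 10% contamination, power is level at ICC 0.02 (both about 72%) and higher at the other two.

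The contamination point makes this a trade-off, but the plan already accepts mixed clinics under its non-disclosure rule, and the balance turns against the change only if contamination is fairly strong and clinics differ little.

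**Conclusion.** The concern holds as one of chance imbalance and uncounted variance, not of systematic confounding. As written, the allocation does not guard against clinic imbalance, and the analysis ignores both clinic and the clinician, who is the randomised unit.

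In the illustrated layout the arm difference has a standard error of about 1.84–2.19 points rather than 1.71–1.77. The nominal 5% t test runs at roughly 9–15% (8–12% where qualification strata partly balance clinic) rather than 6–7%. These figures depend on the assumed 20 clinicians in pairs, clinician ICC 0.03 and clinic ICC 0.02–0.10. They shrink with smaller clinic differences or a high share of single-clinician clinics.

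A reader might also infer that balancing by clinic settles the matter. It does not, because the clinician variance still has to enter the analysis. The change should be made, with moderate confidence in the size of its benefit.

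**What to change.** **Randomization.** Before clinicians are randomised, have the independent researcher allocate them in balanced blocks within clinic, pool clinics with a single consenting clinician into one stratum, and keep qualification balanced by minimisation or constrained allocation.

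**Data Analysis.** Replace the independent t test, and the ANCOVA that depends on a significance check, with one baseline-adjusted mixed model with random effects for clinician and clinic and small-sample degrees of freedom. The Mann–Whitney alternative also treats patients as independent, so it should not be the fallback. A fixed clinic effect without within-clinic allocation is a poor substitute, because a one-armed clinic then contributes nothing to the comparison.

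**Cost.** A new allocation list and a rewritten analysis paragraph, with no additional patients and no change to treatment. With few clinicians the small-sample degrees of freedom cost some power, but that is the price of a valid test. State the downside in the protocol: more clinics will contain both arms, so the non-disclosure rule matters somewhat more, and the gain shrinks or reverses if contamination is strong and clinic differences are small. If clinicians have already been randomised, only the analysis change remains open.

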### Eligibility assessment

#### • Clinicians

Health care practitioners who hold recognized qualifications in physiotherapy, exercise physiology (masters degree), chiropractic, osteopathy or certificate 4 training, who are registered to practice in Victoria and who prescribe exercises are eligible to participate.

#### • Patients

At the initial consultation clinicians will use a screening checklist to confirm eligibility. If participants meet the inclusion criteria the participant and their data will be included in the study. Eligibility criteria are reported in Table 1.

**Table 1 T1:** RCT inclusion and exclusion criteria

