## Methods/Design

Monash University SCERH has granted approval for this study (CF08/2015 – 2008000990). The trial will be reported according to the recommendations of the CONSORT Statement [26,27] and the flow of participants through the study is represented in Figure 1. The quantitative study will compare an exercise rehabilitation program informed by a participant preferences questionnaire compared to a program without this guideline for patients with NSCLBP. The qualitative study will evaluate clinician and participant experience. Patients presenting for exercise prescription will be allocated to clinicians who either do or do not use information regarding patient exercise preferences.

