#### • Controlling bias

The RCT design includes key method features that have been recognised as important in minimising bias in clinical trials: true randomisation, concealed allocation, specification of eligibility criteria, blind outcome assessment, blind analysis and intention-to-treat analysis.

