**Inclusion criteria**
• over 18 years of age
• non-specific chronic low back pain: pain in the area extending from twelfth rib to buttock fold +/- leg for > 8 weeks
• receiving exercise prescription
• ability to speak, read and write English

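### The treating clinician, who knows the arm, confirms eligibility after allocation and so decides whose data count; concealment at entry and intention to treat are not assured

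*Protocol article*

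**What the plan says.** The unit of randomisation is the clinician (Randomization, Clinicians): "Clinicians who have consented to participate will be randomly allocated, by computer-generated codes". Patients get their arm through the clinician (Methods/Design): "Patients presenting for exercise prescription will be allocated to clinicians who either do or do not use information regarding patient exercise preferences".

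Reception staff who are unaware of the protocol and aims apply a first checklist and log refusals and ineligible patients (Study population and recruitment, Patients). Patients then consent, complete the outcome measures and the preference questionnaire, and the sealed questionnaire goes to the treating clinician (Concealment, Patients and receptionists).

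Eligibility is settled only after that (Eligibility assessment, Patients): "At the initial consultation clinicians will use a screening checklist to confirm eligibility". The consequence follows in the same paragraph: "If participants meet the inclusion criteria the participant and their data will be included in the study". Table 1 lists "receiving exercise prescription" among the inclusion criteria.

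The Controlling bias section claims "true randomisation, concealed allocation, specification of eligibility criteria, blind outcome assessment, blind analysis and intention-to-treat analysis", and the Data Analysis section repeats intention to treat.

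**The concern.** Allocation concealment has to bind whoever decides that a patient enters. Here that person is the treating clinician, who knows the arm and delivers the intervention. If clinicians in one arm pass or reject borderline patients differently from those in the other, the analysed groups differ in prognosis before treatment starts.

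Intention to treat protects only the set it is applied to. Removing a patient found ineligible after allocation can be compatible with it when the decision rests on facts that predate allocation and is made without knowledge of the arm. The text secures neither condition. If rejected patients are also not followed, their outcomes cannot be recovered in the analysis.

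**Working it through.** **Order of events and knowledge of the arm**

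1. The clinician's arm is fixed by randomisation before any patient is seen (Randomization).
2. Reception screens, obtains consent and collects baseline. Staff and patients do not know the arm (Study population and recruitment; Concealment).
3. The envelope goes to the treating clinician, so by the consultation the patient is linked to an arm.
4. The clinician knows the arm. In the questionnaire group, "The envelope will only be opened by the clinicians allocated to the questionnaire group". In the control group, "Group 2 clinicians do not use the exercise preferences questionnaire and will return the unopened envelope to a secure storage box in the reception area". The Blinding section asks clinicians only not to disclose it.
5. That clinician completes the deciding checklist (Eligibility assessment).

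Concealment therefore holds at step 2 and is lost at step 5, where entry is decided. Most criteria in Table 1 are facts that predate step 3, such as age, pain duration, pregnancy and fracture. Some, such as nerve root compromise, need clinical judgement. Receiving an exercise prescription can be an event after step 3.

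**Possible size (illustration only)**

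The plan gives no rate of exclusion at the consultation, so there is no stated figure to reproduce. Inputs from Sample Size: SD 10, target difference 5, 75 recruited per group. Assumed: no true effect; a fraction f with the worst predicted outcome is excluded in one arm only; the clinician's prediction correlates ρ with the actual outcome.

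- Shift of the arm mean = ρ × SD × φ(z)/(1 − f), with z = Φ⁻¹(1 − f).
- For f = 0.10: z = 1.2816 and φ(z) = 0.1755, so the shift is ρ × 10 × 0.1755/0.90 = 1.95ρ. This gives 1.95 at ρ = 1 and 0.58 at ρ = 0.3.
- SE = 10 × √(1/75 + 1/(75(1 − f))), which is 1.68 at f = 0.10.
- Two-sided false-positive rate = Φ(−1.96 + shift/SE) + Φ(−1.96 − shift/SE), which is 21.3% at f = 0.10 and ρ = 1.

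| f excluded | Patients of 75 | Shift, ρ = 0.3 | False positive | Shift, ρ = 1 | False positive |
|---|---|---|---|---|---|
| 5% | 3.8 | 0.33 | 5.4% | 1.09 | 10.1% |
| 10% | 7.5 | 0.58 | 6.4% | 1.95 | 21.3% |
| 15% | 11.2 | 0.82 | 7.7% | 2.74 | 36.3% |

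Against the 5-point target, the shifts are 7 to 16% at ρ = 0.3 (0.33/5 to 0.82/5) and 22 to 55% at ρ = 1 (1.09/5 to 2.74/5). The false-positive rates are approximate: they keep the SD at 10 after selection and ignore clustering by clinician.

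**The case against.** The best defence has three parts, and much of it stands.

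First, the clinician only confirms a screen already made by staff unaware of the aims, at clinics that offer exercise programmes. The Protocol protection section also trains the researchers involved in screening. Few patients may be left to discretion, and most criteria leave little room for it. This limits the risk, but the clinician's check still decides inclusion.

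Second, the Concealment section is addressed to patients and receptionists and does protect them. Clinician codes are concealed in sealed opaque envelopes, and nowhere does the article claim that clinicians are masked. A reader might infer a flat contradiction of concealment and intention to treat. The text supports less: a gap at the point of entry, which leaves the general claims in Controlling bias unsecured.

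Third, a reader might infer that reading the preferences changes whether exercise is prescribed, and hence who qualifies. The documents do not say so. Responses are to inform the prescription, the order of checklist and envelope is not given, and the criterion may simply describe the clinic population. What remains is that the wording permits a post-allocation reading, and that clinicians know their arm whether or not the envelope is open.

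Two further inferences go too far. A shift of 20 to 30% of the target follows if 10 to 15% are dropped and do 10 points worse than the rest (0.10 × 10 = 1.0; 0.15 × 10 = 1.5), but that gap is a full SD and is assumed. That no later analysis could repair the harm is true only if rejected patients are not followed. Baseline is collected before the consultation, so rejected and retained patients can at least be compared by arm.

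**Conclusion.** The concern holds as a defect in the entry procedure. As written, a person who knows the arm makes the final decision on who is analysed, after consent, baseline and linkage to a clinician. Entry is not concealed from that person, and intention to treat is not assured.

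The documents show a risk of selection bias, not its size. Under one-sided exclusion of 5 to 15%, the shift runs from about 0.3 to 0.8 points with weakly predictive judgement to 1.1 to 2.7 points with perfect selection. The upper range is a bound, not an expectation. Equal exclusion in both arms, or exclusion unrelated to prognosis, would give no such shift in expectation. The sequence of events is certain from the text; the exclusion rate and the correlation are assumptions.

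**What to change.** - Define trial entry as signed consent plus completed baseline at reception, before the envelope goes to the clinician.
- Apply the exercise criterion at reception, worded as presenting for exercise prescription, as the Methods/Design section already has it.
- Follow everyone who enters and analyse them in the arm of their allocated clinician.
- Have the clinician complete the checklist before opening or returning the envelope.
- Allow removal from the intention-to-treat set only for a listed exclusion that existed before consent and is confirmed by existing staff masked to arm.
- Report consultation-stage exclusions with reasons by arm, and run a sensitivity analysis that keeps these patients in.

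The cost is a change of wording, a checklist review, and outcome collection to 52 weeks for a few extra patients by the phone, SMS and post already planned. Keeping some patients who get no exercise prescription dilutes the effect slightly. Masked review of a checklist that the unmasked clinician filled in reduces discretion but does not remove it, so the main protection is early entry with full follow-up.
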